However, in further understanding the functionality of reward‐related processed in AN, the dopaminergic system is a potentially critical factor, considering both its potent role in reward learning processes (Keiflin & Janak, 2015; Wise, 2004) and its sensitivity to weight loss and food restriction (Frank et al., 2019). For instance, animal studies have illustrated that food restriction and weight loss drive a sensitization of brain reward pathways (Avena et al., 2008; Carr, 2007; Carr et al., 2003) and dopaminergic neuronal activity (Oinio et al., 2017). This adaptive sensitization of D1 and D2/D3 receptors in response to food restriction is thought to drive greater motivation to forage and seek food (Frank et al., 2019). In keeping, the dopamine‐mediated prediction error response is elevated in the NAc, head of the caudate, and insula in underweight adolescents with AN, although this appears to normalize upon weight restoration (DeGuzman et al., 2017).

Thus far, the methods used to interrogate the dopaminergic system in AN have been limited to positron emission tomography (PET) and single‐photon emission computed tomography (SPECT) studies. One novel method of indexing dopaminergic activity, which may be less acutely sensitive to food restriction and weight loss, is neuromelanin‐sensitive magnetic resonance imaging (NM‐MRI). Neuromelanin, which is a byproduct of dopamine and catecholamine synthesis, is found in dopaminergic neurons in the substantia nigra and in the noradrenergic neurons of the locus coeruleus (Graham, 1979). The oxidation of cytosolic dopamine, advanced by ferric iron, reacts with cytosolic proteins and is polymerized, which yields an undegradable iron–melanin–protein complex (Graham, 1979). Following macroautophagy and fusion with lysosomes, these neuromelanin organelles accumulate over the lifespan and are not subject to proteasome degradation (Graham, 1979). As such, neuromelanin is likely not acutely affected by acute weight loss and food restriction—which therefore offers a novel window into assessing the cumulative activity of the dopaminergic system in midbrain regions. Of relevance to AN, single‐unit recordings in response to both (i) food and (ii) conditional stimuli signaling food delivery have been observed in dopaminergic neurons in the substantia nigra (Ljungberg et al., 1992; Mirenowicz & Schultz, 1994, 1996), underscoring the role of nigrostriatal dopaminergic pathways in food‐related reward processing.

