With these considerations, we extended a recently developed multimodal Pavlovian appetitive conditioning study in underweight and weight‐restored AN (WRAN) (Murray et al., 2022), to include the assessment of midbrain neuromelanin in the substantia nigra. Specifically, in addition to indexing the acquisition, extinction, spontaneous reinstatement, and recovery of associative reward learning across multiple units of analyses including subjective experience (self‐report), physiology (heart rate deceleration and pupillary dilation), neural response (brain activity in reward systems), and white matter structural connectivity (from diffusion‐weighted MRI) (Murray et al., 2022), we will also undertake baseline NM‐MRI. In avoiding the use of any cues that may have already acquired a negative valence in those with AN (e.g., food cues), our appetitive conditioning paradigm (Murray et al., 2022) will employ positively valenced, socially rewarding yet symptom‐neutral infant laughter sounds at the US, which adolescents with AN typically rate positively (Murray et al., 2022). The study aims to assess (i) group differences in NM‐CNR in the substantia nigra pars compacta (SNpc) among underweight restricting‐type AN (AN‐R) patients, weight‐restored AN‐R (WRAN‐R) patients, and age‐matched HCs, (ii) assess the extent to which NM‐CNR in the SNpc accords with illness duration among those with AN, (iii) assess the extent to which NM‐CNR in the SNpc accords with blood oxygen level dependent (BOLD) activity in nodes of the reward circuit during the acquisition of positively valenced associations, (iv) assess the extent to which NM‐CNR in the SNpc accords with structural connectivity in the reward circuit, and (v) assess the relationship between NM‐CNR in the SNpc and self‐reported AN trait appetitive motivation. With empirical findings noting stable sex differences in associative learning, the proposed study will include only female participants.

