We hypothesize that (1) compared to controls, those with both acute AN and WRAN will demonstrate reduced NM‐CNR in the SNpc; (2) NM‐CNR in the SNpc will be associated with illness duration in both the underweight (e.g., current illness duration to date) and WRAN (e.g., overall illness duration) groups, respectively; (3) there will be an association between NM‐CNR in the SNpc and subjective appetitive motivation on the behavioral activation scale (BAS) across participants; and (4) there will be an association between NM‐CNR in the SNpc and structural connectivity (as indexed by FA) between VTA/SNpc and the NAc across participants. Lastly, (5) we will undertake exploratory assessments of the concordance between NM‐CNR in the SNpc and BOLD response in the NAc and SNpc during the acquisition stage of our conditioning paradigm, without a priori hypotheses.

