### Participants

2.2

In keeping with our parent study^47^, participants will be female adolescents and young adults (aged 12–22 years), who are (1) acute and underweight AN (*N* = 30), (2) WRAN (*N* = 30), and (3) age‐matched HCs (*N* = 30). All participants will undergo structural NM‐MRI, diffusion MRI, and fMRI during appetitive conditioning. Additional recruitment and assessment information, such as inclusion and exclusion criteria, are described in detail in Murray et al. (2022).

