#### Analysis plan

2.6.1

Variable transformations prior to subsequent analyses will be determined based on distribution diagnostics and outlier analysis. To test Hypothesis 1, we will conduct an ANCOVA, controlling for age and pubertal development scale (PDS) scores, to compare mean NM‐CNR in the SNpc among AN, WRAN, and HCs. We will use multiple linear regression to test Hypothesis 2, examining associations between NM‐CNR in the SNpc and illness duration in the AN group, using age and PDS scores as covariates of noninterest. To test Hypothesis 3, we will use linear regression, examining associations between NM‐CNR in the SNpc and behavioral activation scale scores from the BIS/BAS across all participants, using age and PDS scores as covariates of noninterest. To test Hypothesis 4, we will use multiple linear regression to examine associations between NM‐CNR in the SNpc and structural connectivity (FA), controlling for age and PDS scores. For the exploratory analysis, we will use multivariate multiple linear regression to examine associations between NM‐CNR and BOLD signal. Dependent variables will be BOLD signal in the SNpc and the NAc from the CS+ versus CS− contrast (first eigenvariate) during the acquisition phase, and independent variables will be NM‐CNR in the SNpc, group (AN, WRAN, HCs), and group × NM‐CNR interaction, with age and PDS scores as covariates of noninterest.

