#### Power analysis

2.6.2

No published studies to date have assessed NM‐MRI in those with AN for estimates of effect sizes. As this is a secondary data analysis, the sample was powered for the primary outcomes for primary hypotheses of the parent study, as previously outlined (Murray et al., 2022). With a sample size of *n* = 30 AN, *n* = 30 WRAN, and *n* = 30 HCs, for Hypothesis 1, we will have power = .8 at alpha = .05 to detect an effect size of *f* = .33 (medium). For Hypothesis 2 (*n* = 30), we will have power = .8 at alpha = .05 to detect an effect size of *f*
^2 ^= .28 (medium). For Hypotheses 3 and 4 (*N* = 90), we will have power = .8 at alpha = .05 to detect an effect size of *f*
^2 ^= .089 (small).

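### Hypothesis 2 covers both patient groups, but its planned test covers only the AN group (n = 30), where age-adjusted duration cannot be told apart from age at onset

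*Protocol article*

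**What the plan says.** The hypotheses at the end of the Introduction predict a link between neuromelanin contrast and "illness duration in both the underweight (e.g., current illness duration to date) and WRAN (e.g., overall illness duration) groups". Duration is thus defined separately for each group. Aim (ii), in the same section, asks how far NM-CNR "accords with illness duration among those with AN".

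Section 2.6.1 (Analysis plan) gives one multiple linear regression for this hypothesis, on "illness duration in the AN group, using age and PDS scores as covariates of noninterest". The same paragraph lists AN, WRAN and HCs as three separate groups. Section 2.6.2 (Power analysis) gives Hypothesis 2 a sample of n = 30 and says "we will have power = .8 at alpha = .05 to detect an effect size of" f² = .28.

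The Introduction also gives the reason for adjusting for age: "these neuromelanin organelles accumulate over the lifespan and are not subject to proteasome degradation". Age at onset is not mentioned anywhere in the article.

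**The concern.** Two things combine.

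- **Coverage.** The hypothesis is stated for two patient groups of 30. The analysis and its power calculation reach only one. A reader of the results would not know whether the WRAN part was dropped, left for later or never planned, and the duration question is tested on half of the available patients.
- **Meaning of the coefficient.** The group that is kept is the one where duration is "current illness duration to date". For someone still ill, that is age at scan minus age at onset. Age has to be in the model, and once it is, duration carries the same information as age at onset. The article presents neuromelanin as a cumulative index, so a significant result invites the reading that longer illness changes neuromelanin. An effect of early onset would give the same result.

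**Working it through.** **1. The plan's own figure.** Inputs from 2.6.2: n = 30, alpha = .05, power = .8, f² = .28. Sidedness is not stated, so an F test of one coefficient is assumed. The model has three predictors (duration, age, PDS), so df = (1, 26) and the noncentrality is f² × n = .28 × 30 = 8.4. Power is 0.797 and the f² detectable at 80% is 0.282. The stated figure reproduces, and it is a figure for one group of 30.

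**2. The identity in the acute group.** Let D = age − onset. Then

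b0 + b1·age + b2·D = b0 + (b1 + b2)·age − b2·onset.

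The duration coefficient is minus the onset coefficient, with the same standard error. Fitted to one simulated data set (n = 30, PDS included):

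| Model | b | t | p | R² |
|---|---|---|---|---|
| duration, age, PDS | -0.5918 | -1.510 | 0.143 | 0.58008 |
| onset, age, PDS | +0.5918 | +1.510 | 0.143 | 0.58008 |

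With intercept, duration, onset, age and PDS together, the design has rank 4 for 5 columns. No linear model in this group can separate the three time variables.

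**3. What the planned test does and does not do.** In 2000 simulated trials per scenario (n = 30, residual SD 1, assumed effects of 0.4 per year for duration or onset and 0.3 per year for age), the planned test rejected in:

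- 0.88 of trials when only duration acted
- 0.87 when only onset acted
- 0.05 when only age acted

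It holds its size but cannot tell the first two apart. Replacing age with onset as the covariate rejected in 0.37 of trials when only age acted, so dropping the age adjustment is no remedy.

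**4. How exact the identity is.** Over 1000 simulated data sets the duration and onset t values correlate at -1.000. With age recorded in whole years the correlation is -0.98. In a WRAN-type group with an assumed 0.2 to 3 years since restoration it is -0.87, and the design has full rank (5 of 5).

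**5. Adding WRAN without onset in the model.** With n = 60 and four predictors (duration, group, age, PDS), df = (1, 55) and the detectable f² at 80% power is 0.1355. As partial correlations: √(.28/1.28) = 0.47 at n = 30, and √(.1355/1.1355) = 0.35 at n = 60. In simulation the duration standard error fell to about 0.70 of the AN-only value, close to √(30/60) = 0.71, and power rose from 0.38 to 0.68. The power values depend on the assumed effect and distributions.

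**6. Adding onset to the pooled model.** Let T be time since restoration (zero in AN), so D = age − onset − T. With age and onset in the model, the duration coefficient is exactly minus the coefficient of T (checked numerically: t = -0.781 and +0.781). When only T acted, this test rejected in about 62% of simulated trials. Its standard error was about 1.75 times that of the AN-only model, and 1.2 to 5.6 times under other assumed spreads of T.

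**The case against.** The strongest defence is that Hypothesis 2 and aim (ii) claim only an association. The planned regression tests that validly: it keeps its size, has the stated power and adjusts for age, as the biology described in the article requires. That stands. A reader might infer from the identity that the analysis fails to answer its stated aim, or cannot show that duration matters at all. The documents do not support this, because nowhere do they promise to separate duration from onset. The confounding is shared by any cross-sectional study of currently ill patients.

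A reader might also infer that pooling with WRAN and adjusting for onset would give a clean test of cumulative illness. It would not: step 6 shows that such a coefficient measures time since restoration.

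The identity is also conditional. It needs linear terms and an untransformed duration counted without gaps. Section 2.6.1 allows transformations, and how duration is recorded is left to the parent protocol, which is not shown. This makes the identity approximate in some versions but does not remove it.

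Finally, n = 30 could mean one regression per patient group. But 2.6.1 names a single group, with a label that the same paragraph uses alongside WRAN, so that reading would have to be written in.

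**Conclusion.** The mismatch in coverage is real. Hypothesis 2 is stated for two patient groups (60 participants), while its analysis and power are stated for one (30). Using both would roughly halve the detectable f², from .28 to about .136, with no new participants or scans.

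The second part is a limit on interpretation and not an analysis error. In the acute group a significant coefficient means longer duration or, equally, earlier onset at a given age. This is exact if duration is age minus onset, linear, untransformed and uninterrupted, and close to exact with whole-year age. Including WRAN loosens the link but does not break it in practice (correlation -0.87 under the assumed times since restoration), so the pooled result also needs cautious wording.

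**What to change.** 1. Test Hypothesis 2 in both patient groups, as the Introduction states. One way is a single regression in AN + WRAN (n = 60) with duration, group, age and PDS, plus a duration-by-group check. Use current duration to date for AN and overall illness duration for WRAN. Restate the detectable effect for that sample (f² about .136).
2. Say in 2.6.1 that the acute-group coefficient will be reported as longer duration or, equivalently, earlier onset at a given age.
3. Do not use an onset-adjusted duration coefficient as the test of cumulative illness. If it is shown, label it exploratory, give its interval, and state that it equals minus the coefficient of time since restoration.

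The cost is a few sentences and one regression on participants already being scanned. The downside is that pooling assumes a similar duration slope in the two groups unless the interaction is examined.

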### Neuromelanin‐sensitive MRI

2.3

NM‐MRI will be acquired with a GE Discovery 3T scanner with a 32‐channel head coil. We will acquire two‐dimensional gradient response echo sequence with magnetization transfer contrast (2D GRE‐MT) (Plane = Oblique; repetition time [TR] = 284 ms; echo time [TE] = 4.1 ms; flip angle = 50°; in‐plane resolution = 0.43 × 0.43 mm^2^; partial brain coverage with field of view [FOV] = 512 × 512 mm; number of slices = 10; slice thickness = 2.5 mm; slice gap = 0 mm; MT offset = 1200 Hz; acquisition time = 08:01 min:s). The image slab will be oriented along the anterior commissure–posterior commissure line, with the top slice approximately 3 mm above the floor of the third ventricle to provide coverage of portions of the midbrain containing the SNpc. Three‐dimensional T1‐weighted images (MPRAGE; 0.8 mm^3^) using HCP Lifespan protocols (humanconnectome.org) will be acquired and used for registration. Both NM‐MRI and T1‐weighted images will be visually inspected for artifacts. Preprocessing of the NM‐MRI will be performed using steps that have previously been shown to have high test–retest reliability (Ljungberg et al., 1992). Specifically, preprocessing will be performed using the Advanced Normalization Tools (ANTs; http://stnava.github.io/ANTs/), which will consist of (1) brain extraction of the T1‐weighted image, (2) co‐registration of the NM‐MRI to the T1‐weighted image in native space, (3) spatial normalization of the T1‐weighted image to standard MNI space through nonlinear registration, (4) application of the estimated transformation (determined in step 3) to the NM‐MR image, and lastly (5) spatial smoothing of the normalized NM‐MRI image using a 1‐mm full‐width half‐maximum (FWHM) 3D Gaussian kernel. For each participant, a mask of the crus cerebri will be created by manual tracing of the NM‐MRI image in MNI space using the Seg3D software (www.seg3d.org).

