### Diffusion MRI

2.4

Diffusion‐weighted images will be acquired with a single‐shot spin‐echo echo planar sequence (TR = 4100 ms, TE = 81.7 ms; flip angle = 90°; FOV = 140 × 140 mm; resolution = 1.7 mm^3^; *b* = 3000, 2000, 1000, and 500 seconds/mm^2^; number of slices = 81; number of directions = 102; acquisition time = 07:11 min:s) in the posterior‐to‐anterior direction. A shortened sequence (number of directions = 6) in the anterior‐to‐posterior direction will also be acquired, resulting in pairs of images with reversed phase‐encoding directions (distortions going in opposite directions) that will be utilized for EPI distortion correction. Diffusion MRI preprocessing will be performed using FMRIB's Software Library (FSL; www.fmrib.ox.ac.uk/fsl/). Preprocessing steps will involve using FSL's TOPUP and EDDY tools to estimate and correct the susceptibility‐induced off‐resonance field and correct eddy/current movements. Additional denoising steps such as outlier replacement (Andersson et al., 2017), slice‐to‐volume movement correction (Andersson et al., 2017), and susceptibility‐by‐movement correction (Andersson et al., 2018) will be applied. Bayesian estimation of diffusion parameters (BEDPOSTX) will be used to model and determine the number of crossing fibers per voxel (Jbabdi et al., 2012). Probabilistic tracking with crossing fibers (PROBTRACKX) (Behrens et al., 2007) will be estimated using VTA/SNpc as a seed region and NAc as the target region. Diffusion tensor model will be fitted using DTIFIT to derive FA maps and (exploratory) mean diffusivity (MD) and radial diffusivity (RD) maps.

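### The Hypothesis 4 regression relates two MRI measures without a head-motion covariate, so residual motion shared by the two scans could produce an NM-CNR/FA association

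*Protocol article*

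**What the plan says.** Hypothesis 4 (Introduction) predicts an association, with no direction given, between NM-CNR in the SNpc and structural connectivity "as indexed by FA) between VTA/SNpc and the NAc across participants". Section 2.6.1 fixes the model as a multiple linear regression to "examine associations between NM‐CNR in the SNpc and structural connectivity (FA), controlling for age and PDS scores". No motion measure appears in this or any other model in the article.

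Motion is treated differently in the two scans:

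- **Diffusion (2.4).** Preprocessing includes "using FSL's TOPUP and EDDY tools to estimate and correct the susceptibility‐induced off‐resonance field and correct eddy/current movements". The next sentence adds outlier replacement, "slice‐to‐volume movement correction" and a susceptibility-by-movement correction.
- **NM-MRI (2.3).** "Both NM‐MRI and T1‐weighted images will be visually inspected for artifacts". The five preprocessing steps that follow are brain extraction, co-registration, normalization, application of the transformation and smoothing. None is a motion correction, and no motion metric or exclusion threshold is given.

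On power, section 2.6.2 states: "For Hypotheses 3 and 4 (*N* = 90), we will have power = .8 at alpha = .05 to detect an effect size of" f² = .089.

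**The concern.** Hypothesis 4 is the only confirmatory hypothesis in which both variables are derived from images. Hypotheses 2 and 3 pair NM-CNR with illness duration and with a questionnaire score, so image degradation cannot enter both sides there in the same way.

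Participants are aged 12 to 22 and must lie still for an NM-MRI scan of 8 min 1 s and a diffusion scan of 7 min 11 s. Suppose that those who move more have a blurred SNpc signal and also some error left in FA after correction. Motion would then be a common cause of both variables, and a regression that omits it would attribute the shared part to NM-CNR. Visual inspection can remove gross failures, but it does not adjust for graded differences among the images that pass. Because the hypothesis has no stated direction, a spurious association of either sign would count as support.

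At stake is the interpretation of a positive result: a link between neuromelanin and tract structure, or in part a difference in how still participants lay.

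**Working it through.** **Inputs from the article.** N = 90, alpha = .05, power = .8 and detectable f² = .089 for Hypothesis 4 (2.6.2). The predictors are NM-CNR, age and PDS, so p = 3 (2.6.1).

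**Input not in the article.** The correlation of motion with NM-CNR and with FA, after age and PDS. It is assumed here over the range .1 to .5.

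**Step 1: reproduce the stated power.** For one coefficient, use the noncentral F with 1 and N − p − 1 = 86 degrees of freedom and λ = f² × N = .089 × 90 = 8.01. Power is 0.799 and the detectable f² at 80% power is 0.0892. The stated figure reproduces with a two-sided test; a one-sided test would give 0.878.

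**Step 2: association induced by shared motion.** If NM-CNR and FA are unrelated except through a common motion variable, with correlations r₁ and r₂, the induced partial correlation is r₁ × r₂ and the induced f² is (r₁r₂)² / (1 − (r₁r₂)²). Example at .4: .4 × .4 = .16, and f² = .0256 / .9744 = .026.

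**Step 3: false rejection rate.** This is a simulation of 40,000 data sets per setting, with N = 90, no true association and r₁ = r₂ = r. The unadjusted test has 86 df and the adjusted test 85.

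| Assumed r | Induced partial r | Induced f² | Rejects, no motion term | Rejects, motion itself in model |
|---|---|---|---|---|
| .1 | .01 | .0001 | 5.1% | 5.0% |
| .2 | .04 | .0016 | 6.5% | 5.0% |
| .3 | .09 | .0082 | 13.3% | 4.9% |
| .4 | .16 | .0263 | 32.2% | 5.0% |
| .5 | .25 | .0667 | 66.2% | 5.1% |

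A separate run of 20,000 data sets gave 6.3%, 13.0%, 31.3% and 65.5% for r = .2 to .5, hence the rounded figures of about 6%, 13% and 31 to 32% for .2 to .4.

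**Step 4: unequal or only partly shared motion.** Only the product matters. If image-level correction weakens the FA path, say r₁ = .4 and r₂ = .2, the induced correlation is .08. If motion in the two scans correlates only .5 and r₁ = r₂ = .4, it is .4 × .4 × .5 = .08 again. Both lie between the .2 and .3 rows, so rejection would fall between 6.5% and 13.3%. These values too are assumptions.

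**Step 5: an imperfect motion measure.** With a proxy of reliability 0.8, rejection is 5.3% at r = .3 and 6.4% at r = .4. With reliability 0.5 it is 7.3% and 12.6%.

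**Step 6: power after the change.** One motion covariate (p = 4) or two (p = 5) leaves power at 0.799 and the detectable f² at 0.0892.

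**The case against.** The strongest reply is that motion has not been ignored. FA is computed after EDDY, outlier replacement, slice-to-volume correction and susceptibility-by-movement correction, all of which should weaken the path from motion to FA. This stands: a reader might infer that the plan makes no allowance for head motion, and section 2.4 shows otherwise. What is missing is a motion term in the regression and any listed correction for NM-MRI.

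Second, the mechanism and its size are not in the documents. The article does not say that motion lowers NM-CNR or that error remains in FA after correction, and it gives no correlation for either. The scans are separate, so only motion common to both counts, and the age term may absorb part of it. This also stands. The upper rows of the table show what would follow from large correlations and are not estimates for this trial.

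Third, section 2.3 says the NM-MRI preprocessing steps have shown high test–retest reliability. That is relevant but does not settle the matter, because a participant who tends to move may do so at every scan.

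Fourth, a condensed article may leave motion thresholds and sensitivity analyses to a fuller document. This is fair for quality-control detail. But the article itself names the Hypothesis 4 covariates, and it defers only recruitment and assessment (2.2) and BOLD acquisition and processing (2.5.2) to the parent protocol. The point is about a covariate set that is stated.

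A reader might also infer that the Hypothesis 1 group comparison is biased. That would need motion to differ between the AN, WRAN and control groups, and nothing in the documents shows that it does. No such claim is made here.

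**Conclusion.** The point holds in a limited form. The Hypothesis 4 regression adjusts for age and PDS only. Motion is corrected at image level for diffusion, and NM-MRI is only inspected visually, so residual motion shared by the two scans could produce an NM-CNR/FA association.

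The documents do not determine how large this is. With equal assumed correlations and one fully shared motion variable, the false rejection rate is close to nominal at .2 or below and becomes material from about .3. It is smaller if the FA path is weakened by correction or if motion is only partly shared. It does not follow that a positive Hypothesis 4 result would be due to motion; the planned model alone simply could not rule that out. The stated power is correct. The change is a worthwhile, inexpensive protection against bias and not the repair of an error in the plan's figures.

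**What to change.** In 2.6.1, add to the Hypothesis 4 regression a per-participant motion summary taken from the EDDY movement estimates, for example mean relative displacement. At the least, pre-specify this as a sensitivity analysis and report the NM-CNR/FA coefficient with and without the term.

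The cost is one degree of freedom (86 to 85) and essentially no power (0.799 before and after). No new scanning is needed. That EDDY can supply such a summary is inferred from its stated use for movement correction; the article does not say so. The summary would describe the diffusion scan and serve only as a proxy for motion during NM-MRI. The adjustment is therefore partial, and the report should say so.

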At the neurobiological level, structural abnormalities in the brain's reward circuitry have been observed in AN, which is evident in both gray matter structures and white matter fiber tracts. Reduced gray matter volume is evident in key nodes of the brain's reward circuit, including the ventral striatum and orbitofrontal cortex (OFC) (Frank et al., 2013; Titova et al., 2013), and aberrant connectivity of white matter tracts in reward systems has also been observed (Cha et al., 2016; Via et al., 2014). In white matter tracts connecting key reward circuit regions of the ventral tegmental area (VTA) and the nucleus accumbens (NAc), we previously found in adolescents with AN abnormal microstructure in the form of reduced neurite and myelin density and reduced orientation dispersion (Murray et al., 2023). Further, orientation dispersion in this tract—a measure of tract “fanning,” which, in general, is negatively correlated with fractional anisotropy (FA) (Zhang et al., 2012)—was associated with subjective reward responsiveness.

With regard to functional activity in the brain's reward circuit, mixed results have emerged from functional magnetic resonance imaging (fMRI) studies of reward‐related tasks to date. In the context of food cues, fMRI studies have generally noted diminished corticostriatal activity in AN (Brooks et al., 2011; Jiang et al., 2019), which extends to the taste, smell, and sight of palatable foods (Holsen et al., 2012; Jiang et al., 2019; McFadden et al., 2014; Oberndorfer et al., 2013). However, other studies suggest *hyperactivity* in reward‐related regions such as the ventral striatum (Cowdrey et al., 2011) and amygdala (Vocks et al., 2010) in response to palatable food cues, despite those with AN implicitly and explicitly stating “liking” and “wanting” these foods less than controls (Cowdrey et al., 2013). In concert, heightened activity in prefrontal regions including the medial prefrontal cortex and dorsolateral prefrontal cortex following exposure to palatable food cues has driven several hypotheses suggesting elevated top‐down inhibition of reward processing (Kerr et al., 2017; Uher et al., 2003; Uher et al., 2004).

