#### Neuromelanin contrast‐to‐noise ratio

2.5.1

NM‐CNR will be calculated as the percent signal difference at each voxel relative to a participant‐specific reference of modal signal intensity in the crus cerebri, a nearby white matter region with minimal neuromelanin content (Cassidy et al., 2019). Average neuromelanin CNR will be extracted for the SNpc based on a probabilistic atlas (Ito et al., 2008).

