#### Structural connectivity

2.5.3

The structural connectivity between the VTA/SNpc and the NAc will be determined as average FA (and as exploratory, MD, and RD) values of the right‐ and left‐averaged projection tract connecting the two regions.

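### Hypothesis 4 is valid as a test of association, but with only age and PDS as covariates it cannot separate a reward-tract link from shared white-matter variation or diagnostic group

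*Protocol article*

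**What the plan says.** - **Hypothesis (Introduction, last paragraph).** NM-CNR in the SNpc is expected to be associated with "structural connectivity (as indexed by FA) between VTA/SNpc and the NAc across participants". Aim (iv) describes this as agreement with structural connectivity in the reward circuit.
- **Tract measure (2.5.3).** Mean FA "values of the right‐ and left‐averaged projection tract connecting the two regions". It is not scaled to whole-brain FA.
- **NM-CNR (2.5.1).** A percent signal difference from a participant-specific reference, the "modal signal intensity in the crus cerebri, a nearby white matter region with minimal neuromelanin content".
- **Model (2.6.1).** NM-CNR is related to "structural connectivity (FA), controlling for age and PDS scores". No whole-brain FA, control tract or group term is listed for this hypothesis. Group appears in the Hypothesis 1 comparison and in the exploratory BOLD model.
- **Background (Introduction).** In AN, "aberrant connectivity of white matter tracts in reward systems has also been observed". The authors also cite their own finding of abnormal microstructure in VTA–NAc tracts in adolescents with AN. Hypothesis 1 expects that "those with both acute AN and WRAN will demonstrate reduced NM‐CNR in the SNpc".
- **Power (2.6.2).** N = 90, power .8, alpha .05, detectable f² = .089.

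**The concern.** Two routes could produce a slope without any particular link between SNpc neuromelanin and this tract.

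1. **Shared white-matter variation.** Raw tract FA includes whatever raises or lowers FA across the brain. NM-CNR is divided by a white-matter signal, and the Introduction says the method relies on magnetization transfer and T1 shortening. White-matter properties could therefore enter both variables. Linear age and PDS may not absorb all of this in females aged 12–22 who range from underweight to healthy. This route can operate within a single group.
2. **Diagnostic group.** The plan expects lower NM-CNR in both patient groups and cites altered reward-tract white matter in AN. Pooling 30 AN, 30 WRAN and 30 controls without a group term lets those two differences appear as a slope across participants.

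What is at stake is interpretation. A significant slope would naturally be read as midbrain neuromelanin relating to reward-circuit connectivity, although the same slope might appear with other tracts or vanish within groups.

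**Working it through.** **1. The plan's own figure.** For one coefficient among p predictors, the test is F(1, N − p − 1) with noncentrality λ = f²·N. With N = 90, p = 3 (NM-CNR, age, PDS) and alpha .05, the detectable f² at power .80 is .0892, and power at f² = .089 is .799. The stated .089 is reproduced. It corresponds to a partial r of √(.089/1.089) = .286.

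**2. Shared-factor route (all loadings assumed).** Let a common white-matter factor correlate b with NM-CNR and a with tract FA, with no other link. The induced correlation is r = a·b, so f² = r²/(1 − r²) and λ = 90·f², tested on F(1, 86).

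For b = .4, a = .5: r = .20, f² = .04/.96 = .0417, λ = 3.75, rejection .48.

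Now add a whole-brain FA covariate that correlates .85 with the factor (also assumed; .85² = .7225). The remaining partial correlation is a·b·(1 − .7225)/√[(1 − .7225a²)(1 − .7225b²)]. For the same case this is .0555/√(.8194 × .8844) = .065, giving λ of about .38 and rejection of about .09.

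Simulation with 4,000 runs per setting and age and PDS in the model agrees:

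| b (NM-CNR) / a (tract FA) | Planned model | With whole-brain FA proxy |
|---|---|---|
| 0 / any | about .05 | about .05 |
| .2 / .3 | .08 | .05 |
| .4 / .5 | .46–.47 | .09 |
| .5 / .7 | .92–.93 | .23–.25 |

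With a fixed at .7, the planned model rejects 5%, 10%, 25%, 50% and 75% of the time at b = 0, .1, .2, .3 and .4. If the factor is unrelated to group, a group term alone does not help: 25% and 49% at b = .2 and .3. A perfectly measured global covariate holds rejection near 5%.

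**3. Group route (shifts assumed).** Set b = 0 and shift both NM-CNR and global white matter down in AN and WRAN. The planned model rejects 6.6%, 10.1% and 13.2% of the time at shifts of .5, .7 and .8 SD. Adding either group or global FA returns it to about 5%. If the group difference were confined to reward tracts, whole-brain FA would not capture it and only the group term would.

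**4. Cost in power.** Whole-brain FA takes one degree of freedom and group takes two, so p rises from 3 to 6 and residual df falls from 86 to 83. At f² = .089 power goes from .7991 to .7988, and the detectable f² is .0893. This is for a given partial effect. In simulations where the factor loads on tract FA but not on NM-CNR, adding whole-brain FA raised power for a true tract link (.75 to .83 in one assumed setting, .76 to .91 in another), because it removes residual variance.

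**The case against.** **No specificity claim is made.** A reader might infer that Hypothesis 4 asserts a link peculiar to this tract, so that the rejection rates above are type I errors of the planned test. The text does not support that. It predicts an association and does not say the link is absent elsewhere. With an induced r of .20 the two variables are associated, and the test detects this correctly. This objection stands: the weakness lies in what a positive result can be taken to mean.

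**The common factor is assumed.** A reader might also infer that the documents show brain-wide white-matter variation entering NM-CNR. They show only a possible route. The reference is signal intensity in one region, not FA, and nothing given ties it to whole-brain FA. The Introduction's white-matter evidence concerns reward tracts in patients, not brain-wide variation between individuals. This also stands, which is why the range is wide and includes no inflation.

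**Group is the better-documented source.** This is correct. It argues for adding the group term, not for leaving the model as it is. A group term does not address variation within groups, so both additions are needed.

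**A fuller analysis plan may cover this.** Sensitivity analyses are often left to such a plan. Section 2.6.1 nevertheless states the covariates hypothesis by hypothesis and includes group in the BOLD model but not here.

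**Adjustment may cost power or fail.** The power objection does not stand (step 4). The second part does: at loadings of .5/.7 about 23% rejection remains after adjustment.

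**Conclusion.** The point holds as a limit on interpretation. The planned model is a valid test of association and no stated figure is wrong. It cannot distinguish a link with the VTA/SNpc–NAc tract from white-matter variation shared by tract FA and a white-matter-referenced NM-CNR, or from group differences in both.

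The size is unknown. With no tract-specific link, the planned test rejects about 8% (loadings .2/.3) to 93% (.5/.7), stays at 5% if the factor does not load on NM-CNR, and rejects about 7% to 13% for group shifts of .5 to .8 SD. All loadings, shifts and the .85 proxy correlation are assumptions. The recommendation rests on the documented route, the missing group term and the small cost of a second model, not on any one of these percentages.

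**What to change.** In 2.6.1, keep the planned Hypothesis 4 model and pre-specify a second one that adds:

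- mean whole-brain white-matter FA, excluding the target tract, from the DTIFIT maps already planned;
- group (AN, WRAN, HC), as in the exploratory BOLD model.

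Report both NM-CNR slopes with confidence intervals. Describe the result as a reward-tract link only with the adjusted slope shown beside it. If the slope vanishes on adjustment, report it as not distinguishable from a brain-wide or group-related association.

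**Cost.** Three degrees of freedom, one extra value per participant and a few sentences of text; no new data. If the true link is brain-wide, the adjusted slope will be smaller. The group term also removes any between-group part of the association, which is why the planned across-participant slope should stay in the report. Adjustment reduces strong confounding but does not remove it, and the write-up should say so.

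**Optional.** FA in the crus cerebri, and the same regression on one control tract outside the reward circuit. Crus FA would need the FA maps registered to MNI space, where 2.3 has the mask traced.
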